### Risks or limitations and viability

Some of the studied variables may not be collected in the digital clinical history, which is the main data source. To solve this limitation and considering that patients have to attend necessary to INR controls in the health center, the missing data will be recovered using a clinical interview. Furthermore, we could experience low group meeting attendance due to lack of interest or lack of motivation of the studied individuals. Patients who do not attend a meeting will be called again to participate in the next group session. “Hawthorne effect” could occur namely when patients feel that they are being observed, it forces them to comply with the advices in a more strict way. Furthermore, the main investigator will attend the intervention group meetings, which may result in bias when he interprets the outcomes.

The research will be carried out under usual clinical practice. The intervention that will be performed is strictly educative. Potential side effects are associated with patient risks linked to anticoagulant drug intake.

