#### Study design

Randomized single-blind controlled trial.

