### Description of the intervention

The study will be carried out over a 28-month period. It started on 1 September 2018, and it will finish on 31 December 2020. Participants will be contacted by phone. Trial information with details will be explained to them, and they will be asked whether they are interested in taking part. At the same time, they will be scheduled for the group meetings. Signed informed consent forms will be obtained when the patient attends the health center before the group meetings begin. Patients in each strate (PCC) will be randomly distributed to the intervention group or the control group (a random numbers table will be used). The allocation sequence will be generated by the researcher team. The allocation concealment mechanism consists of organizing patients considering their Andalusian Health Service Number of Clinical Record (AHNCR). After assignment to an intervention, participant names will be deleted by the nurses in charge of the recruitment in order to mask the data. The outcome assessors will not know the patients’ identity. The masking will be carried out by replacing the patients’ identification data with an assignment number.

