All patients under study will receive an information sheet, and they will sign informed consent forms when they attend to INR control appointments. The investigators will try to encourage the involvement of every person so that patients included in the intervention group will be telephoned in previous weeks in order to achieve attendance at group meetings (at least three times and at different times if necessary) by a nurse. They will be recalled the day before the meeting as a reminder. After that, the intervention will be carried out and it will be based on the patients’ attendance of an educational session led by an expert patient (a member of the “Málaga anticoagulated patients association”). This person had been previously trained by health professionals and is able to take on a leadership role as an instructor, providing support through their knowledge and experience. Written material and a questionnaire form were developed for the intervention group before the meeting (Anexo VII). The patients are asked to answer questions about their vitamin K antagonist knowledge. Then, the expert patient will answer this question for everyone “what obstacles could we find when trying to reach an appropriate anticoagulation?” The instructor will rely on the support of short PowerPoint presentations as well as on graphic material explaining the subjects to the patients. The main explanations for inappropriate control values will be provided by the expert patient: other drug consumption, inadequate food, adherence to treatment, etc. Brainstorm, Phillips technique 6.6, role playing, and a table including main ideas provided by the patients will be used to assist them in keeping their INR levels in an appropriate range, and the impediments they face will be addressed. All of this will complement the knowledge transmitted by health professionals. A sanitary professional will carry out observations and energizer tasks if necessary.

Group meetings with educational sessions will be organized in a primary health center, and they will take place from Monday to Thursday in the evenings (according to the convenience of the center) with at least 90 min each. It has been estimated that eleven sessions are necessary, including 15 persons each as a maximum in order to complete one session per person. The sessions will all be held in the same classroom and under the management of the expert patient and the observation of the main researcher.

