#### Data collection

Plans to collect variables will consist of an analysis of the digital medical records in order to obtain the patients’ clinical information. Meetings have been carried before the beginning of the research among the researchers to unify data collecting criteria. Data collecting forms are available as attached documents to this protocol. All of the variables detailed below will be collected as long as they are suitably listed in the digital medical history or could be directly obtained from the patient during the medical interview, without the need for changing the health center’s usual clinical practice, over the 6 months prior to the intervention. Any data required to support the protocol can be supplied on request. The data will be collected on the collection sheets and kept by the principal investigator as follows.

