### Timetable and work program

The study is being carried out over a 28-month period. The assembly of the project took place on 1 day at the Primary Care Center *Ciudad Jardin* practice classroom for all healthcare members involved in the research, along with the expert patient who will execute the intervention. The nurses will explain to the participants about the study approach, and they will collect the consent forms from the participants.

In the first step, at the start of the study, a retrospective data collection of the 6 months prior to the intervention will be completed from all patients who meet the selection requirements and are included in the AOT program. Once the anticoagulated patients have been analyzed and the list of the patients on inappropriate control has been completed, a random sampling will be done in every health center in order to build two groups: *intervention group and control group*.

The intervention group will include the indicated patients. Nurse students will take on the telephone calls to schedule intervention group patients for group meeting attendance. The main researcher and the expert patient will attend every group meeting, but the researcher will act just as an observer. Every participant center will rely on nurses (10 partners) and two resident medical interns (learning Family and Community Medicine) to complete this task. Due to their frequent contacts with anticoagulated patients, the nurses will instruct them about study issues and will collect the signed written consent forms; also, they will be involved in data collecting, INR figures, and patient study variables.

A portfolio with the collected data forms will be distributed to every participant. It will be employed by the patients to collect their data, which will be transcribed to a digital book. This book will be identical for every participant center and it will be used as a basis for the randomization. Two resident medical interns will handle all of the computerized recordings.

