**Fig. 2 Fig2:**
[figure not shown]
Timetable

An analysis to check the proper operation of the intervention will be made following the first group meeting.

The data monitoring committee is comprised of the main researcher ([name]) and doctors [name] and [name]. All researchers will have access to the final data set. The results will be reported to the participants within 6 months after the statistical analysis is completed. This committee is independent of the sponsor, and funding is not provided under any terms or competing interests.

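### The main researcher observes every intervention session, and the protocol admits this may bias his interpretation of the outcomes, yet it sets no safeguard and describes masking of identity only

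*Protocol article*

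**What the plan says.** The Study design section gives the design as "Randomized single-blind controlled trial". The only masking is described under Description of the intervention: "The outcome assessors will not know the patients’ identity", and "The masking will be carried out by replacing the patients’ identification data with an assignment number". Both statements concern who the patient is. Neither says that the assigned group is hidden.

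The Timetable and work program section states: "The main researcher and the expert patient will attend every group meeting, but the researcher will act just as an observer". Description of the intervention also places the sessions under his observation, and it says that control patients attend none of them.

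On the data, the Data collection section states: "The data will be collected on the collection sheets and kept by the principal investigator as follows". On the consequence, Risks or limitations and viability concedes that "the main investigator will attend the intervention group meetings, which may result in bias when he interprets the outcomes". The text then moves on without naming a countermeasure.

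**The concern.** Patients know whether they went to a group session, so any single blind in this trial has to lie with those who assess and analyse the outcome. Removing names protects that blind only from people who do not already know who was allocated where. Someone who has sat through every session does know, at least for those who attended.

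What is at stake is how far a positive result can be trusted. The INR values are objective, but turning them into a between-group comparison involves choices. If those choices, or the interpretation, are open to a person who knows the arms, a reader cannot rule out that this knowledge influenced the result. The protocol recognises this risk and leaves it open.

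**Working it through.** No sample size, power or error rate is at issue, so the check sets the statements side by side, with one small calculation.

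1. **What is masked.** Description of the intervention: identity, through an assignment number. No statement covers allocation.

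2. **What attendance reveals.** Only intervention patients attend, so anyone seen at a session is known to be in the intervention arm.

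3. **How much of the arm this covers.** Inputs: 156 per group (sample size, Step II), and eleven sessions of at most 15 people (Description of the intervention).
   - Sessions needed: 156 / 15 = 10.4, rounded up to 11. This reproduces the stated number.
   - Places: 11 × 15 = 165, which is at least 156.
   - The sessions are thus sized for the whole intervention arm, and the main researcher attends all of them. He sees every intervention patient who comes. He does not see non-attenders, and the Risks section expects that attendance may be low.

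4. **His contact with data and results.** The principal investigator keeps the sheets (Data collection). The main investigator interprets the outcomes (Risks or limitations). The text after Fig. 2 gives all researchers access to the final data set, with no condition that the arms stay coded.

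5. **Where knowledge of the arm could enter.** The primary outcome may be scored as the percentage of INR values in range or as Rosendaal time in range (Primary outcome measure). Losses have to be classified (Step II), and one of the two descriptions there counts failure to attend scheduled meetings. If that means the group meetings, only intervention patients can be lost in this way. The document does not say who takes these decisions.

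6. **Separation that does exist.** Nurses take part in data collection, and two residents handle the computerised records (Timetable and work program). Nothing says that either group is masked to the arm or that they calculate the outcome.

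Steps 1 to 4 show one person who knows the allocation of all attenders, has custody of the sheets and interprets the results. Step 6 offers only partial separation.

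**The case against.** The strongest reply is that the protocol blinds outcome assessors and never names the main researcher as one. An unblinded interpreter does not contradict blinded assessors. The outcome comes from INR measurements taken at usual controls, and the risk is openly listed as a limitation. A fuller protocol or analysis plan might say who calculates time in range and on what data.

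Most of this stands, and it limits the finding. A reader might infer that the assessor blind necessarily fails because of him. The documents do not support that, since no section gives him outcome scoring or loss classification. Custody of the sheets is not scoring either, and the text does not say whether the sheets carry names or only the assignment number.

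A reader might also add his seat on the committee ("The data monitoring committee is comprised of the main researcher") as a further breach of the blind. That seat bears on the committee's independence from the trial team, and the text claims independence only from the sponsor. It says nothing about who scores the outcome.

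A further tempting inference is that a stand-in observer is already available, because "A sanitary professional will carry out observations and energizer tasks if necessary". The condition at the end of that sentence means that no standing observer is assured.

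The reply does not remove the core. The document itself assigns session attendance and outcome interpretation to one role, states that bias may follow, and names no protection. Disclosing a bias does not control it.

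**Conclusion.** The concern holds as an admitted and unmitigated risk of bias in data handling and interpretation. It does not show that the assessor blind is broken, and it does not show that any result would be biased.

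Its size cannot be stated. The document gives neither a standard deviation for time in range nor any basis for assuming how far an unmasked person might shift it, so converting the risk into an inflated error rate would only reflect whatever was assumed. What can be stated is the reach: the main researcher knows the allocation of every intervention patient who attends, out of 156 planned.

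The verdict rests on one assumption: that main researcher, main investigator and principal investigator are the same person. That is the natural reading, but it is not stated. If the sheets are kept by someone else, the data-handling part weakens. The conflict between attendance and interpretation remains, because the Risks section states it for a single person.

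**What to change.** Amend Description of the intervention, Data collection, and Risks or limitations and viability so that:

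- allocation as well as identity is masked in the analysis data set, with the arms shown only as A and B;
- calculation of time in range, classification of losses and the between-group comparison are done on that coded data set by existing team members who neither attended sessions nor scheduled patients for them;
- the main researcher takes no part in these steps and interprets the results only after the coded-arm results are final.

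He can still attend the sessions as observer. The residents should not be assumed to qualify for the masked work. The Timetable section mentions them directly after the scheduling calls and group meetings, and says that the digital book underlies the randomisation, so they may know the allocation too.

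The cost is a change of wording and some reassignment of tasks, provided that the team includes people who meet the condition. The downside is that the main researcher gives up early sight of the data.

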### Timetable and work program

The study is being carried out over a 28-month period. The assembly of the project took place on 1 day at the Primary Care Center *Ciudad Jardin* practice classroom for all healthcare members involved in the research, along with the expert patient who will execute the intervention. The nurses will explain to the participants about the study approach, and they will collect the consent forms from the participants.

In the first step, at the start of the study, a retrospective data collection of the 6 months prior to the intervention will be completed from all patients who meet the selection requirements and are included in the AOT program. Once the anticoagulated patients have been analyzed and the list of the patients on inappropriate control has been completed, a random sampling will be done in every health center in order to build two groups: *intervention group and control group*.

The intervention group will include the indicated patients. Nurse students will take on the telephone calls to schedule intervention group patients for group meeting attendance. The main researcher and the expert patient will attend every group meeting, but the researcher will act just as an observer. Every participant center will rely on nurses (10 partners) and two resident medical interns (learning Family and Community Medicine) to complete this task. Due to their frequent contacts with anticoagulated patients, the nurses will instruct them about study issues and will collect the signed written consent forms; also, they will be involved in data collecting, INR figures, and patient study variables.

A portfolio with the collected data forms will be distributed to every participant. It will be employed by the patients to collect their data, which will be transcribed to a digital book. This book will be identical for every participant center and it will be used as a basis for the randomization. Two resident medical interns will handle all of the computerized recordings.

After that, the intervention will be carried out and it will be based on the patients’ attendance of one meeting lead by an expert patient. Due to the lack of space and in order to improve the patient understanding, and according to the convenience of the center, the meeting will be performed on different evenings but always in the same classroom and under the management of the expert patient and the observation of the main researcher. The last step will consist of collecting INR control data. INR control data will be obtained within 6 months from the activity date in both groups (control group and the intervention group). Then, a new assembly of the researchers’ team will be carried out. Once this period expires, a comparative before-after statistical study of every studied subject and between the intervention and control group will be performed (Fig. 2).

**Fig. 2 Fig2:**
[figure not shown]
Timetable

An analysis to check the proper operation of the intervention will be made following the first group meeting.

The data monitoring committee is comprised of the main researcher ([name]) and doctors [name] and [name]. All researchers will have access to the final data set. The results will be reported to the participants within 6 months after the statistical analysis is completed. This committee is independent of the sponsor, and funding is not provided under any terms or competing interests.

### Legal and ethical issues

This project will be performed respecting the principles of the Declaration of Helsinki (Fortaleza Revision. 2013) and Good Clinical Practice. Personal data will be treated following European Parliament Resolution 2016/679 and 27th of April of 2016 Council with concerns of personal data treatment and protection.

The study protocol was approved by the research ethical committee which belongs to the General Healthcare Area of Málaga, prior to initiation of patient recruitment on 26 March 2015.

Data confidentiality is always an imperative condition, and the data use was strictly conducted to reach the protocolized aims and to notify the relevant authorities.

Protocol amendments will be reported to the research ethics committee and to funding foundation (FIMABIS) and trial sponsor ([name]).

## Data Availability

Available upon justified request to the author.

## Abbreviations

DAOA: Direct action oral anticoagulants
VKA: Vitamin K antagonists
HC: Health center
AF: Atrial fibrillation
AH: Arterial hypertension
BMI: Body mass index
INR: International normalized ratio
AOT: Oral anticoagulant therapy
TRT: Time in therapeutic range
